#### Implementation

After satisfaction of inclusion criteria and completion of baseline questionnaires, participants will be randomised at a 1:1 ratio to the treatment intervention or waitlist-control arm, adjunctive to their treatment as usual. Randomisation will be completed by the project coordinator using the REDCap randomisation module.

The project coordinator will inform the participant of their group allocation following randomisation and determine their availability to commence sessions if allocated to the therapy arm. The participant will be assigned to a therapist based on matching availability. Participants randomised into the waitlist control group will be reminded of the trial timeline and opportunity to access therapy after 32 weeks.

#### Blinding

Unblinded parties include participants, trial therapists, medical monitors and the project coordinator. Trial therapists will be blinded, however, to participant responses on follow-up self-report questionnaires. They will not have access to Week 10, Week 20 and Week 32 visits in the REDCap participant self-report questionnaire project.

Statisticians will be blinded to participant group assignment while the trial is active. They will become unblinded after database lock.

### Statistical methods

A detailed statistical analysis plan describing the analysis of the feasibility and clinical outcomes will be prepared prior by the trial statisticians to unblinding the database for analysis. All outcomes will be summarised. Descriptive statistics will consist of numbers and percentages for categorical variables. Mean and SD or median and interquartile range (25th–75th percentiles) will be reported for continuous variables. The frequency and percentage of participants with missing data will be provided for all outcomes. Following a mixed-methods convergent parallel design, quantitative data and qualitative data will be analysed separately and results compared with identify how they confirm, contradict or expand on each other.^37^

#### Feasibility outcomes

For binary feasibility markers in table 1, the exact (Clopper-Pearson) method will be used to obtain the two-sided 95% CIs.

#### Clinical outcomes

As the trial is a feasibility and pilot study, reporting of clinical outcomes will be mostly descriptive. Any hypothesis testing between the treatment groups will be limited and will therefore be interpreted alongside the magnitude and direction of the treatment effect estimate and two-sided 95% CI. No adjustment for multiple testing will be implemented due to the non-confirmative nature of the trial. Subgroups (eg, female/male, prior therapy, mode of delivery) will be explored using descriptive statistics only.

Suitability of a clinical outcome measure for a future trial will be gauged via the quantitative analysis outlined earlier and the qualitative analysis of the semi-structured feedback interviews aimed to explore the therapies benefit and potential mechanisms of action. Feedback interview transcripts will be analysed following inductive thematic analysis, as the authors have previously employed.^38^ Assumptions about the pooled SD of the proposed clinical outcome will be derived descriptively, including a two-sided 95% CI for the pooled SD

#### Safety outcomes

AEs will be summarised descriptively by treatment group, including the number of AEs and the number of participants with at least one AE. Summary statistics will be presented for the full measure and for each of the factors of the NEQ.

#### Exploratory outcomes

Among the participants who consent to the neuroimaging component, task-based fMRI run, whole-brain analyses will be employed to determine task-relevant regions of Blood Oxygen Level Dependent signal change using statistical parametric maps computed in SPM12 or other neuroimaging software. Region-of-interest analyses may be additionally employed to interrogate the data. Resting-state fMRI data will be assessed using connectivity analyses. Task-based and resting-state fMRI data will be compared between the pretreatment (baseline) and post-treatment timepoints.

A preliminary evaluation of the likely cost-effectiveness of the therapy will be carried out from partial societal and health sector perspectives drawing on the Assessment of Quality of Life 8-dimension scale (AQoL-8D) utility data, additional outcome measures (ie, Depression Anxiety Stress Scale, 21 item (DASS-21)) and information on health service use and lost productivity collected through a self-report RUQ. The within trial economic evaluation will estimate the cost to deliver the therapy through microcosting. The additional resource use collected through the RUQ will be valued using standard Australian unit costs, and lost productivity will be valued using an average wage rate plus overhead costs. The economic evaluation will first measure and value any change to the use of healthcare resources over the period of the study between the ACT and wait-list groups. Any additional costs associated with the therapy will be compared with the outcomes achieved. Quality-adjusted life years will be derived from the AQoL-8D that will form a cost-utility analysis and the other primary and secondary outcome measures will be used for the cost-effectiveness analysis. Standard economic evaluation techniques will be used including calculation of incremental cost-effectiveness ratios (ICERs) and using non-parametric bootstrapping to determine CIs for ICERs. Sensitivity analyses will be used to determine the impact of varying important study parameters (such as unit cost price variation).

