### Sample size

#### Sample size estimation

A total of 120 randomised participants is planned to provide adequate precision around the assumption of the primary feasibility outcome and to potentially inform the assumption of the pooled SD needed to work out the sample size of a future trial that is aimed to demonstrate the effect of the therapy. Assuming 120 participants are randomised, if study completion (ie, retention) is observed for 60% of these participants (72/120), then the two-sided 95% CI of the true underlying retention rate is (51%, 69%). The exact (Clopper-Pearson) method was used to obtain the 95% CI. For continuous (normally distributed) outcomes, a sample size of 70 in total (35 per treatment group) is considered sufficient to estimate the pooled SD with reasonable precision.^34^ Regarding the feedback interviews, sampling will continue until theoretical saturation is reached. A review of 100 studies analysing interview data demonstrated that 25 interviews were sufficient to achieve theoretical saturation.^35^ Thus, we anticipate that 25 participants who complete the therapy will be interviewed, and their transcripts analysed.

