#### Power calculations

The trial is a pilot and feasibility study and is not designed to detect a treatment effect. As a result, the sample size justification is precision-based and no power calculation was performed.^34^

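### A bootstrap CI on the ICER is the only sampling-uncertainty summary named for the economic evaluation, and it is likely to be unreadable unless the QALY effect is about half an SD or more

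*Protocol article*

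**What the plan says.** The Exploratory outcomes section under Statistical methods describes a preliminary cost-effectiveness evaluation of therapy against waitlist. QALYs come from the AQoL-8D, which Table 2 schedules at baseline and weeks 10, 20 and 32. ICERs will be calculated, "using non-parametric bootstrapping to determine CIs for ICERs". Sensitivity analyses are also planned, but these vary inputs such as unit prices. For sampling uncertainty the ICER interval is the only summary named.

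On effect measures, the same section says that "the other primary and secondary outcome measures will be used for the cost-effectiveness analysis". A few sentences earlier it gives the additional outcome measures as the DASS-21, introduced by ie rather than eg.

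Power calculations states that the trial "is not designed to detect a treatment effect" and that "the sample size justification is precision-based and no power calculation was performed". Sample size estimation says "A total of 120 randomised participants is planned", and Implementation that "participants will be randomised at a 1:1 ratio". No expected QALY difference, utility SD, cost difference or cost SD appears anywhere.

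**The concern.** An ICER is a cost difference divided by an effect difference, so it is discontinuous where the effect difference is zero, and its sign is ambiguous. A negative value arises when the therapy is cheaper and better, and also when it is dearer and worse.

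Suppose the therapy costs more. A bootstrap replicate with a slightly negative QALY difference then gives a large negative ratio, which sorts to the bottom of the list. In decision terms it is among the least favourable replicates and belongs beyond the top. Once such replicates make up more than 2.5% of the total, they take over the lower 95% limit, and the interval mixes opposite conclusions.

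The Introduction lists preliminary cost-effectiveness data among the things the trial may help provide. In a trial not sized for an effect, the one uncertainty summary named could turn out unusable for that purpose.

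**Working it through.** **Reproducing the plan's own figure.** The only sample-size calculation is the exact (Clopper-Pearson) 95% CI for 72 of 120 retained. Beta quantiles give 50.7% to 68.8%, matching the stated 51% to 69%. That calculation is sound, but it concerns retention and says nothing about precision for QALYs.

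**Inputs from the protocol.** 120 randomised 1:1 gives 60 per arm. The illustrative 60% retention gives 72, or 36 per arm if retention is equal between arms (an assumption). The 36 is a low case: it supposes that only retained participants contribute QALYs.

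**Assumed input.** The standardised QALY difference d (difference divided by QALY SD), varied because the protocol gives none.

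**Formula.** With n per arm, the expected z-statistic for the QALY difference is z = d / √(2/n). The share of replicates at or below zero exceeds 2.5% when the observed z is below 1.96. The chance of that is Φ(1.96 − z).

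For example, with d = 0.2 and n = 60: √(2/60) = 0.1826, z = 1.10, and Φ(1.96 − 1.10) = 0.81. With n = 36: √(2/36) = 0.2357, z = 0.85, and Φ(1.11) = 0.87.

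| d | 60 per arm | 36 per arm |
|---|---|---|
| 0.2 | 81% | 87% |
| 0.3 | 62% | 75% |
| 0.4 | 41% | 60% |
| 0.5 | 22% | 44% |
| 0.8 | 1% | 8% |

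The chance is one half at d = 1.96 × √(2/n), which is 0.36 with 60 per arm and 0.46 with 36. Holding it to 20% needs d = (1.96 + 0.8416) × √(2/n), which is 0.51 or 0.66.

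**Simulation check.** 400 simulated trials per scenario, each with 2,000 bootstrap replicates, assuming a QALY SD of 0.1, a cost difference of 3,000 and a cost SD of 4,000. The simulated shares of trials with more than 2.5% of replicates at or below zero were close to the table: at d = 0.2, 80% and 85%; at d = 0.5, 22.5% and 41%; at d = 0.8, 1% and 9% (60 and 36 per arm).

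A Fieller interval for a ratio is bounded only when the denominator differs clearly from zero. It was bounded in 18% and 14% of trials at d = 0.2, in 77% and 57% at d = 0.5, and in 99% and 91% at d = 0.8.

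**On the money scale, 60 per arm, same assumptions.**
- d = 0.2: true ICER 3,000 / (0.2 × 0.1) = 150,000 per QALY; median percentile limits about −1.2 million to +1.4 million.
- d = 0.5: true ICER 3,000 / (0.5 × 0.1) = 60,000; median limits about 18,000 to 203,000.
- d = 0.8: true ICER 3,000 / (0.8 × 0.1) = 37,500; median limits about 17,600 to 75,000.

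The first interval cannot be interpreted. The last can.

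**The case against.** A reader might infer that the replicates are bound to straddle zero and that the interval will be meaningless however the data fall. The documents do not support that. They give no QALY effect or SD, and if the effect is large the interval is usually readable: at d = 0.8 the problem arises in only 1-8% of trials. Nor is the fault in bootstrapping or in the sample size, which is reasonable for a feasibility trial. It lies in the summary chosen.

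It can also be said that the section presents ICERs and the bootstrap within an open list of standard techniques, does not specify percentile limits, and is a condensed account. Handling of quadrants, planes and acceptability curves may be in a fuller plan. This stands in part: the absence of those items is no fault in itself. But the article does commit to a CI on the ICER, and adding other summaries would not make that interval readable when replicates cross zero. Any interval formed by ordering the ratios shares the difficulty, and a Fieller interval is then unbounded.

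The analysis is exploratory, no decision rule uses the interval, and incremental costs, QALY differences and a point ICER can be reported in any case. This stands and keeps the point minor.

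Finally, because the primary outcome is retention, a reader might infer that a cost per retained participant is planned. No sentence says so. The mention of primary measures may be a loose reference back to the AQoL-8D and DASS-21.

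**Conclusion.** The concern holds as a minor one. The protocol commits to an uncertainty summary that works only if the QALY effect turns out fairly large, in a trial not designed to show an effect. An uninterpretable interval is more likely than not below a standardised QALY difference of about 0.36 (60 per arm) or 0.46 (36 per arm). At 0.5 it is a substantial risk, and at 0.8 a small one.

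These figures rest on a normal approximation, equal retention by arm and an assumed range for d. The monetary limits rest further on the assumed QALY SD and costs and are illustrations only.

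The wording on primary and secondary measures is a separate, smaller inconsistency within one section. Retention, the primary outcome in Table 1, is not a health effect, so the wording should be reconciled with the earlier statement that confines the additional measures to the DASS-21.

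**What to change.** Keep the bootstrap and change what is reported from it:

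- Incremental net monetary benefit with 95% CIs at willingness-to-pay values stated in advance, a cost-effectiveness plane and an acceptability curve. All three remain valid when the QALY difference is zero or negative.
- The ICER as a point estimate, with a CI only if the replicates do not cross zero effect. This condition is stricter than the 2.5% threshold: in the simulation at d = 0.5 with 60 per arm, 73% of trials had at least one of 2,000 replicates at or below zero. The ICER will therefore often stand without an interval.
- Name the effect measures for the cost-effectiveness analysis explicitly, so that the two statements in Exploratory outcomes agree.

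The cost is a few sentences in the analysis plan. No new data or extra resampling is needed. The one real demand is that willingness-to-pay values be named before unblinding.

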#### Treated waitlist outcomes

In addition to the above-described analysis in all participants using data collected up to and including Week 32, an observational analysis is planned on all data of the waitlist controls who elect to do the therapy. To explore changes over time in treated waitlist controls from baseline up to and including Week 20 post first therapy session, descriptive statistics will be provided at each study visit. For clinical outcomes, these summaries may be complemented with an analysis using a mixed linear regression model that accounts for the longitudinal nature of the data. The feasibility of this statistical analysis will be informed by the sample size among those waitlisted who elect to do therapy. This model will provide estimates, two-sided 95% CIs and p-values of within-group changes in clinical outcomes while waiting and subsequent within-group changes in clinical outcomes following therapy after waiting. Any hypothesis testing will be limited and will therefore be interpreted alongside the magnitude and direction of the treatment effect estimate and two-sided 95% CI. No adjustment for multiple testing will be implemented due to the exploratory nature.

### Data collection and management

Study data will be collected and managed using REDCap electronic data capture tools hosted at The University of Melbourne. This includes participant self-report questionnaires, therapy attendance details, the Transdiagnostic Clinical Global Impression scale and AEs. All data stored in REDCap will be in a re-identifiable format.

The trial therapists will audio record each session with their participants so the therapists’ adherence to the treatment manual and competency can be independently assessed. In addition, treatment feedback interviews will be audio recorded and transcribed using Zoom software and cross-checked by study staff to ensure accuracy of the transcript. All audio recordings and transcripts will be stored on a Records Managed Sharepoint hosted by The University of Melbourne. Hard copy data, including consent forms, clinician notes and the MINI, will be stored in individual participant files in a locked filing cabinet in the Department of Psychiatry, Austin Hospital, VIC, Australia.

All data will be kept for a minimum of 7 years postpublication of the primary paper. After this time, destruction of hard copy data, participant medical records, consent forms and investigator site files will be advised by the Sponsor, Austin Health, and actioned by the Principal Investigator as required. However, non-identifiable datasets used for statistical analysis will be kept in perpetuity to facilitate data sharing and open-access policies as encouraged by the NHMRC (excluding participants’ data where consent for data sharing was not provided).

### Patient and public involvement

Patients and patient representatives were involved in the codesign of the intervention, in the modified Delphi process that produced the case definition, and in the conduct of the trial by representation on the steering group.

## Ethics and dissemination

### Research ethics approval

The study will request ethics approval from Austin Health HREC. Additional amendments to the protocol, PICF, advertising material, etc, will be submitted to the committee for review prior to implementing desired changes, except in the event of urgent safety measures where immediate actions to reduce risk will be implemented.

### Dissemination policy

Publications and supplementary materials will be uploaded into the University of Melbourne Minerva Access repository and Austin Health Research Online repository (author accepted manuscripts where necessary). All publications will follow the International Committee of Medical Journal Editors authorship eligibility guidelines.

A lay, HREC-approved summary of the primary study results will be communicated to participants directly, if desired. A copy of this summary will also be uploaded onto the study’s clinical trial registry listing (Australian New Zealand Clinical Trials Registry; ANZCTR) and provided to the Australian Government Department of Health’s Tick bite diseases and symptoms attributed to tick bites website.

Participants may provide extended consent for their data to be shared to related projects approved by a registered HREC. Data will be provided in a non-identifiable format. A metadata listing will be created in The University of Melbourne’s Melbourne Academic Centre for Health figshare repository outlining the type of data available and requirements to follow before it can be shared (eg, receipt of HREC approval letter to conduct the project).

## Data Availability

Data are available upon reasonable request.
